### Interim analysis and monitoring

2.8

Because this is a short-term, single-arm, pilot study, we will not conduct interim analysis for the clinical efficacy of ALA-PDD-ULA. However, the safety of interventions will be independently evaluated by the Data and Safety Monitoring Committee at the time as follows:i)Critical modification of the study protocol is requiredii)Any serious adverse event associated with this agent occursiii)A critical problem is observed while monitoringiv)The principal investigator needs the judgment of this committee

Moreover, the monitoring committee independently evaluates whether the study is implemented in compliance with the study protocol, and the data are appropriately corrected according to a pre-arranged monitoring plan at the time when the first patients have been enroled and once per year.

### Protocol of Fluorescence In Situ Hybridization (FISH) assay

2.9

As exploratory research, we evaluate the diagnostic accuracy of UroVysion test of voiding urine specimens during follow-up and upper urinary tract irrigation or catheterized urine obtained by URS. Sample preparation is performed according to the protocol for UroVysion® FISH bladder cancer assay (SRL, Inc., Tokyo, Japan). We transfer urine sediments into ThinPrep® PresevCyt® Solution containing 55% methanol (UV7) and subject fixed samples to the SRL laboratory. Trained observers who are blinded for clinicopathologic data assess enumeration of FISH signals. This assay enables the visualization of molecular alterations, including aneuploidy of chromosomes 3 (red), 7 (green), and 17 (aqua) and loss of locus 9p21 (gold), which are frequently seen in human bladder cancer. Specimens are considered to be positive for UroVysion test if four cells or more have a gain of 2 or more chromosomes (3, 7, or 17) or 12 cells or more have a loss of both copies of locus 9p21 among observed 25 morphologically abnormal cells [18,22].

### Statistical analysis

2.10

Descriptive statistics will be computed for all study variables. EZR 1.54 (Saitama Medical Center, Jichi Medical University, 2020) and PRISM software version 7.00 (GraphPad Software, Inc., San Diego, CA, USA) were used for statistical analyses and data plotting, respectively. A two-sided P value of less than 0.05 will be considered to be statistically significant.

The full analysis set population and the per protocol set population will be separately analyzed for both the primary endpoint (two-year PFS rate) and survival outcomes listed in the secondary endpoints (Fig. 1). The per-protocol set population will be analyzed for the other secondary endpoints. The PFS of study population will be estimated by Kaplan Meier method, and 95% confidence interval (CI) will be calculated using Greenwood's formula for variance. When the lower limit of 95%CI of two-year PFS rate is more than 58% (threshold survival rate), the ALA-PDD-ULA is considered superior to the conventional ULA without PDD assistance. When the lower limit of 95%CI of two-year PFS rate is 58% or less, the ALA-PDD-ULA is considered not superior to the conventional ULA without PDD assistance. In addition, a sensitivity analysis of the primary endpoint will be performed using the Fine-Gray subdistribution hazard regression. This model considers patients who die of other causes (competing events) before recurrence or progression.

The amount of change in other post-operative observations over time will be analyzed using the repeated measures analysis of variance, Wilcoxon signed-rank sum test, or Mann-Whitney *U* test as appropriate. Mixed-effects models for repeated measures will be applied to detect multiple change-points in longitudinal data. To evaluate the diagnostic accuracy of UroVysion test, the result is compared to the pathological diagnosis obtained by URS biopsy. The sensitivity, specificity, positive predictive value, negative predictive value, and diagnostic accuracy are determined according to standard methods [23]. The sensitivities of UroVysion test and the combination with the conventional cytology are compared to that of conventional cytology alone using McNemar's test.

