**Methods:**

The FLUAM trial is a prospective, single-center, single-arm pilot trial to investigate the efficacy of 5-aminolevulinic acid-mediated photodynamic diagnosis (ALA-PDD)-assisted ULA for localized UTUC and the usefulness of the UroVysion® assay (multiprobe fluorescence in situ hybridization) as a monitoring test after the kidney-sparing treatment. After the screening and registration, a total of 20 patients with localized UTUC will undergo the initial ALA-PDD-assisted ULA followed by the second look ALA-PDD-assisted ureteroscopic examination. The primary endpoint is progression-free survival. Secondary endpoints include patient reported outcomes, diagnostic accuracy of UroVysion assay to detect tumor recurrence, adverse events, and safety of the intervention.

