### Follow-up schedule and data collection

2.6

Patient data will be collected before and after the surgery; 1, 3, 6, 9, 12, 15, 18, 21, 24, and 27 months after the initial ALA-PDD-ULA; and at the end of the trial (Fig. 3). To improve monitoring adherence, the clinician will take time to explain the need for post-operative surveillance examination, including second-look URS, and encourage the participants to undergo routine cystoscopy, urine cytology, and CT/CT-U/MRI. The assessment includes patient-reported outcomes, such as the SF-8™, EORTC QLQ-C30, FACT-BL, International Prostate Symptom Score (IPSS), and overactive bladder symptom score (OABSS). The postoperative observational evaluation such as PROs can be discontinued upon participant request. The data will be documented in specific Case Report Forms for complete blood count, serum chemistry, cystoscopy, urine cytology, CT/CT-U/MRI, genitourinary adverse events (AEs), and other possible AEs using the Common Toxicity Criteria for Adverse Events (CTCAE v 5.0). When recurrence is suspected in imaging examinations, ALA-PDD-ureteroscopy is considered and, if recurrent tumor is present, ALA-PDD-ULA is additionally performed. AEs strongly related to the intervention of ALA-PDD-ULA are listed as follows: “Intraoperative urinary injury,” “Urinary tract infection,” “Fever,” “Renal hemorrhage,” “Hematuria,” “Creatinine increased”, “Urinary frequency”, “Photosensitivity”, “Hepatobiliary disorders”, “Urinary tract pain”, “Urinary urgency”, and “Dysuria”. Any other potential AEs are recorded and grouped into ‘related AEs’ or ‘unrelated AEs.’ When serious AEs occur, investigators report to the Safety Monitoring Committee.

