### Sample size setting

2.7

The primary endpoint of this trial is progression-free survival (PFS). Progression is noted when patients experience either of the following events: A) Imaging with CT scan or MRI reveals local progression or distant metastasis (event occurrence date: date of the imaging) and B) The physician judges that ureteroscopic treatment cannot be completed in the follow-up ALA-PDD-assisted ureteroscopy (event occurrence date: date of the ureteroscopy). The date of the initial ALA-PDD-ULA is taken as the starting point. The historical data of the Department of Urology and Andrology, Kansai Medical University Hospital was obtained from consecutive patients undergoing ULA without PDD assistance. The 2-year progression-free survival (PFS) rate of ULA without PDD assistance and that with PDD assistance was 58% and 90%, respectively. The required sample size was determined to test our null hypothesis of superiority in the 2-year PFS rate after the initial surgery. Assuming that the threshold survival rate is 58% and expected survival rate is 90%, 14 patients are required with a 3-year registration period and 2-year tracking period years to provide 90% power (β = 0.10) and an α level of 0.05 (two-sided). Given the 20–30% proportion of ineligible patients, a total of 20 trial cases will be enroled in this study. We calculated the sample size using Statistical Tools 2019 provided by Cancer Research and Biostatistics (https://stattools.crab.org/).

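### Section 2.10 assigns adverse events and safety to the per-protocol set, so the reported safety analysis can leave out patients who were exposed to the intervention

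*Protocol article*

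**What the plan says.** The abstract (Methods) sets out the endpoints: "Secondary endpoints include patient reported outcomes, diagnostic accuracy of UroVysion assay to detect tumor recurrence, adverse events, and safety of the intervention". The Introduction names safety, beside efficacy, as something the trial will investigate.

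Section 2.10 (Statistical analysis) then assigns populations in two sentences. The first covers the primary endpoint and the survival outcomes among the secondary endpoints: "The full analysis set population and the per protocol set population will be separately analyzed for both the primary endpoint (two-year PFS rate) and survival". The second covers everything else: "The per-protocol set population will be analyzed for the other secondary endpoints". Adverse events are not survival outcomes, so the second sentence governs them. The article names no safety set or all-treated set and makes no exception for safety.

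Three other statements touch on safety or on analysis in general, but none sets a population for the safety analysis:
- Section 2.6, on data collection: "Any other potential AEs are recorded and grouped into ‘related AEs’ or ‘unrelated AEs", with serious events reported to the committee.
- Section 2.8, on monitoring: "the safety of interventions will be independently evaluated by the Data and Safety Monitoring Committee" when certain triggers occur.
- Section 2.10, opening sentence: "Descriptive statistics will be computed for all study variables".

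**The concern.** A safety analysis should describe everyone exposed to the intervention. A per-protocol set, in the usual meaning of the term, keeps only those whose course followed the plan. The two can part company here for reasons linked to harm. Section 2.6 lists intraoperative urinary injury and renal haemorrhage among the events expected from the intervention. Either could lead to an aborted procedure or a missed second-look ureteroscopy, and the second look is part of the planned course. Photosensitivity and hepatobiliary disorders, also listed, can follow ALA intake whether or not the ablation goes to plan.

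If membership of the analysed set depends on the outcome being measured, the reported rate is biased. A single-arm trial has no comparator that would reveal the distortion, and with about 20 patients one or two exclusions move a rate visibly. The article expects its results to change the standard of care, so readers will take the published adverse event rates as the risk of the technique.

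**Working it through.** **1. Which population applies.** Adverse events and safety are secondary endpoints (abstract). Section 2.10 gives two populations to survival outcomes and one, the per-protocol set, to the other secondary endpoints. Since safety is not a survival outcome, its population is the per-protocol set. This step needs no arithmetic and does not depend on the power calculation.

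**2. The plan's own numbers.** Section 2.7 states "14 patients are required with a 3-year registration period and 2-year tracking period years to provide 90% power (β = 0.10) and an α level"; the test is two-sided at 0.05. It enrols 20: "Given the 20–30% proportion of ineligible patients". Two one-arm exponential calculations (58% versus 90% at 2 years, 3 years' accrual, 2 years' follow-up) give 12 on the cube-root hazard scale and 16 on the hazard scale, so 14 lies between them. The inflation reproduces: 14 / (1 − 0.30) = 20 exactly, and 14 / (1 − 0.20) = 17.5, rounded up to 18.

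**3. Assumed size of the two sets.** The article does not say how many treated patients will fall outside the per-protocol set. For illustration, I take all 20 as treated and the 20–30% allowance as the loss: 20 × 0.80 = 16 and 20 × 0.70 = 14. At the other end, if every patient outside the per-protocol set is never treated, the two sets coincide and nothing is lost.

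**4. Precision.** With zero events in n patients, the exact two-sided 95% upper limit is 1 − 0.025^(1/n). The chance of seeing at least one case of an event with true rate p is 1 − (1 − p)^n.

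| n analysed | Upper limit, zero events | At least one case, p = 10% | At least one case, p = 5% |
|---|---|---|---|
| 20 | 16.8% | 87.8% | 64.2% |
| 16 | 20.6% | 81.5% | 56.0% |
| 14 | 23.2% | 77.1% | 51.2% |

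**5. Direction and range of bias.** Suppose 4 of 20 treated patients have a given event, a rate of 20%.
- If all four are among those excluded, the per-protocol rate is 0/16 or 0/14, that is 0%.
- If none is excluded, it is 4/16 = 25% or 4/14 = 28.6%.

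The error can therefore run either way. The zero extreme is very unlikely if exclusion is unrelated to harm: with 6 of 20 excluded at random, the chance that all four cases are among them is C(16,2) / C(20,6) = 120 / 38,760 = 0.3%. A strong downward bias thus needs exclusion tied to the event, which is the mechanism described above.

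**The case against.** The strongest reply is that harm is not lost. Adverse events are recorded without restriction to the per-protocol set, serious ones go to the committee, and the committee reviews safety independently. This stands for monitoring. It does not settle the final analysis, because collection and event-triggered review do not set the denominator of the reported rates. The promise of descriptive statistics covers all variables but names no population, so it does not override the specific per-protocol sentence.

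A second reply is that the article does not define the per-protocol set, so nothing shows that an injury, an aborted procedure or a missed second look leads to exclusion. That is correct, and the article need not carry the definition. The point rests on the usual meaning of the term and on the contrast with the full analysis set, and it claims only that such patients can be left out.

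Three stronger readings are tempting and are not supported:
- A reader might infer that the plan itself expects to drop 4–6 of 20 treated patients from the safety table. The 20–30% in section 2.7 is an allowance for ineligible patients. Eligibility is settled before enrolment (sections 2.2 and 2.3), and some of these patients may never be treated. They would then be absent from an all-treated set too.
- A reader might infer that the complication rate will be understated. Step 5 shows that it can also be overstated.
- A reader might extend the same criticism to patient-reported outcomes and diagnostic accuracy. The case there is weaker. Participants may stop the questionnaires on request, so missing data would remain in a full analysis set. The UroVysion work is described as exploratory and is already limited to comparison with biopsy pathology.

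**Conclusion.** The point holds for adverse events and safety. The article states a population for these endpoints, and it is the wrong one for safety; this is not detail left to an analysis plan. As written, patients who received ALA or started the procedure can be left out of the reported safety analysis for reasons that may depend on the harm. The bias is plausibly downward but could be upward.

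The loss of precision ranges from none, if the per-protocol and treated sets coincide, to the n = 14 row of the table. At that end the zero-event upper limit moves from 16.8% to 23.2%, and the chance of seeing a 10% event at least once falls from 88% to 77%. Those figures assume that all 20 patients are treated and that the ineligibility allowance equals the loss of treated patients. The conclusion about the population does not need either assumption. The primary endpoint, its decision rule and the sample size are unaffected.

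**What to change.** Amend section 2.10 to take adverse events and safety out of the per-protocol sentence. State that they are analysed in all patients who received ALA or started the procedure, whatever happened afterwards. Per-protocol safety results, if shown at all, should be labelled as supportive.

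The cost is one sentence in section 2.10, with any full protocol or analysis plan brought into line. The adverse events are already to be recorded under section 2.6, so no new data, visits or patients are needed.

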**Conclusion:**

The goal of this trial is to determine the potential benefit of ALA-PDD assistance in patients who undergo the ULA. The evidence of this novel technique is still limited. The results are expected to change the standard of care and lead to better management of localized UTUC.

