### Study type and ethical issues

2.1

This clinical trial is a prospective, single-center, single-arm trial for patients with localized UTUC, which is ongoing at Nara Medical University Hospital. This trial complied with the Declaration of Helsinki regarding investigation in humans. Its ethical clearance and the final study protocol (version 1.0 on June 21st, 2021), including the subject information, informed consent forms, and associated documents, were approved by the Certified Review Board of Nara Medical University (institution ID: CRB5200002). Informed consent and written consent forms of patients are mandatory before study participation. This clinical trial was prospectively registered with the Japan Registry of Clinical Trials on June 28th, 2021 (the reference number: jRCTs051210042). The URL of trial registry record is found in https://jrct.niph.go.jp/latest-detail/jRCTs051210042.

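### The primary decision rule turns exceeding a fixed 58% in one arm into superiority over conventional ULA, a treatment the trial does not compare, and event B as worded applies only under PDD

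*Protocol article*

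**What the plan says.** The trial has one arm, "which is ongoing at Nara Medical University Hospital" (section 2.1). Section 2.7 gives the origin of the reference: "The historical data of the Department of Urology and Andrology, Kansai Medical University Hospital was obtained from consecutive patients undergoing ULA without PDD assistance". It then states: "The 2-year progression-free survival (PFS) rate of ULA without PDD assistance and that with PDD assistance was 58% and 90%, respectively". The 58% becomes the threshold and the 90% the expected rate. This gives 14 patients, raised to 20 for ineligibility.

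Section 2.7 defines progression as either (A) local progression or metastasis on CT or MRI, or (B) the physician's judgement that "ureteroscopic treatment cannot be completed in the follow-up ALA-PDD-assisted ureteroscopy".

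Section 2.10 estimates two-year PFS by Kaplan-Meier with a Greenwood 95% interval. If the lower limit is above 58%, "the ALA-PDD-ULA is considered superior to the conventional ULA without PDD assistance"; if it is 58% or less, the treatment is considered not superior. Section 2.8 calls the trial a pilot, while the Conclusion says: "The results are expected to change the standard of care".

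**The concern.** The test and its stated conclusion do not match. The test sets one group of patients against a number; the conclusion ranks two treatments. To get from one to the other, the 58% would have to be what these patients, at this hospital and with this endpoint, would have achieved without PDD. The rule takes that as known exactly, although the figure was estimated in other patients at another centre and has sampling error of its own.

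Event B adds a second gap. As worded it needs a follow-up PDD ureteroscopy, so half of the composite definition cannot be applied literally to patients managed without PDD. It is also a judgement made by investigators who know the treatment (section 2.2).

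At stake is what a positive result may be said to mean. Under the rule as written, 14 to 20 patients clearing a reference would be reported as superiority over conventional ULA, in an article that looks ahead to a change in standard care.

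**Working it through.** **Inputs.** Threshold p0 = 0.58, expected rate p1 = 0.90, 90% power, two-sided α = 0.05, 3-year registration, 2-year tracking, 14 patients required, 20 enrolled (section 2.7). Rule: lower 95% Greenwood limit above 0.58 (section 2.10). Assumptions of this check: every patient is followed to two years, and limits are untransformed unless stated, because the article names no transformation.

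**1. The plan's own sample size.** With exponential survival and the stated registration and tracking periods, two-sided 0.05 and 90% power, standard one-sample formulas give 11.8 (log-hazard scale), 11.3 (one-sample log-rank) and 15.04 (hazard scale), that is 12, 12 and 16 patients. The simple binomial formula n = [(z_α√(p0(1−p0)) + z_β√(p1(1−p1)))/(p1−p0)]² gives [(1.645×0.4936 + 1.282×0.300)/0.32]² = 13.98, or 14, at one-sided 0.05, and 17.8, or 18, at two-sided 0.05. Then 14/(1−0.30) = 20. The stated 14 and 20 are reproduced within 2 patients by the survival formulas and are not in dispute.

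**2. What passing requires.** With complete data the Greenwood standard error is √(p(1−p)/n).
- n = 14: 11/14 gives 0.786 − 1.96×0.1097 = 0.571 (fails); 12/14 gives 0.857 − 1.96×0.0935 = 0.674 (passes).
- n = 20: 15/20 gives 0.750 − 1.96×0.0968 = 0.560 (fails); 16/20 gives 0.800 − 1.96×0.0894 = 0.625 (passes).

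**3. Chance of declaring superiority when PDD adds nothing.** Let q be the two-year PFS that these patients would have without PDD under the trial's event definition. The article does not give q, so a range is shown. The chance is P(X ≥ r), with X binomial (n, q).

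| q | n = 14, r = 12 | n = 20, r = 16 |
|---|---|---|
| 50% | 0.6% | 0.6% |
| 58% | 2.9% | 3.5% |
| 65% | 8% | 12% |
| 70% | 16% | 24% |

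With log-log limits the cut-offs become 13/14 and 17/20. The chances for n = 14 are then 0.1%, 0.5%, 2.1% and 4.7%, and for n = 20 they are 0.1%, 1.0%, 4.4% and 10.7%.

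**4. Sampling error in the 58%.** The article gives no cohort size. For assumed sizes of 30, 50 and 100, the 95% Wilson interval around 58% is 40–74%, 44–71% and 48–67%. Most of the range in step 3 therefore lies within ordinary sampling error of a modest series, in both directions, before any difference in patients or centre.

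**5. Event definition.** Component A can be ascertained in any cohort that was imaged. Component B, read literally, can occur only at a PDD-assisted follow-up ureteroscopy, and the reference cohort is described as treated without PDD. The article does not say how progression was defined in that cohort.

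**6. What a comparative claim would need.** A concurrent 1:1 comparison of 58% with 90% (two-sided 0.05, 90% power) takes [1.96√(2×0.74×0.26) + 1.282√(0.58×0.42 + 0.90×0.10)]²/0.32² = 37.4, or 38 per arm and 76 in all, against 20 in one arm here.

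**The case against.** The strongest reply is that a single-arm pilot tested against a prespecified threshold is an accepted design, openly declared, and that at exactly 58% the rule's false-positive rate is close to nominal (2.9–3.5% against 2.5% in the upper tail). That stands. Neither the design nor the sample size is at fault; only the conclusion attached to the test is.

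A reader might go further in four ways that the article does not support.

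- **That the reference cohort could not have been on the trial's endpoint.** The historical definition is not stated, component A applies to any imaged cohort, and the substance of component B could be recorded at any follow-up ureteroscopy. The mismatch lies in how B is worded.
- **That the rule is biased in favour of PDD.** Criterion D (a single tumour of 10 mm or less) may select better-prognosis patients, but criteria A, C and E (solitary kidney or bilateral tumour, patients unfit for nephroureterectomy, patients who decline it against advice) may do the reverse. PDD at follow-up may reveal more disease, while unblinded judgement may lower the event count. The 16–24% at q = 70% is one assumed case and must be read beside the 0.6% at 50%.
- **That the 90% has no basis.** The article does not say that it came from the non-PDD series, and a condensed article may leave its source, and the details of the cohort, to the full protocol.
- **That the second look explains any gain.** Trial patients "undergo the initial ALA-PDD-assisted ULA followed by the second look ALA-PDD-assisted ureteroscopic examination", but whether the reference patients also had a second look is not stated.

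The forward-looking sentence about standard care is not an analysis rule either, and the text next to it says that evidence is still limited.

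**Conclusion.** The point holds as a fault in the stated conclusion of the primary analysis. Exceeding 58% shows that PFS in this cohort is above a prespecified reference; it does not show superiority to ULA without PDD. Event B as worded ties part of the endpoint to the PDD procedure and so does not transfer to the reference cohort.

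The error attached to a superiority claim is not the nominal one but depends on an unknown: 0.6% to 16% with 14 patients and 0.6% to 24% with 20, for PFS without PDD between 50% and 70%. These figures rest on complete two-year follow-up and untransformed limits; log-log limits give 0.1% to 4.7% and 0.1% to 10.7%. The sign of any bias cannot be determined from the article. Confidence is high on the mismatch between test and conclusion and on the wording of event B. That the 58% was in fact measured on a different endpoint is not established.

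**What to change.** In section 2.10, replace the conclusion with: *If the lower limit exceeds 58%, two-year PFS is higher than the prespecified historical threshold and a controlled comparison is warranted; superiority to ULA without PDD is not claimed.* Change the companion sentence to match: *If the lower limit is 58% or less, the trial has not shown that two-year PFS exceeds the threshold.* Bring the Conclusion into line.

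For the analysis, word event B without PDD: *ureteroscopic treatment cannot be completed at follow-up ureteroscopy*. This lets one definition serve both cohorts. It does not remove the possibility that PDD changes what is seen at follow-up, and the report should say so.

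Report the 58% with its cohort size, 95% interval and event definition. Keep 58% as the prespecified threshold, since recruitment is under way and recomputing it would replace the null hypothesis. Re-tabulating the historical cohort under the common definition is useful only as a supportive analysis, and only if patient-level data are available; the article does not show that they are.

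The cost is a few sentences and a more modest claim. The sample size is unchanged.

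### The Fine-Gray regression named as sensitivity analysis gives hazard ratios, not a 2-year rate to set against 58%, and its event wording does not match the primary endpoint

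*Protocol article*

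**What the plan says.** Section 2.1 describes the design: "This clinical trial is a prospective, single-center, single-arm trial for patients with localized UTUC". Section 2.7 defines the PFS event in two parts. Event A is "Imaging with CT scan or MRI reveals local progression or distant metastasis". Event B is the physician's judgement, at follow-up ureteroscopy, that ureteroscopic treatment cannot be completed. Neither death nor a recurrence that can be treated again is listed. Section 2.6 provides for a recurrent tumor to receive a further ablation.

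The sample size in 2.7 rests on one absolute rate against a fixed threshold: "Assuming that the threshold survival rate is 58% and expected survival rate is 90%, 14 patients are required".

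Section 2.10 estimates PFS by Kaplan-Meier with Greenwood's variance. Superiority is declared when the lower 95% limit of the 2-year rate is above 58%. The section then adds that "a sensitivity analysis of the primary endpoint will be performed using the Fine-Gray subdistribution hazard regression", and explains: "This model considers patients who die of other causes (competing events) before recurrence or progression". It gives no covariate, no comparison group and no link to 58% for this model. The historical patients supply the threshold, and the article does not say that they enter the regression.

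**The concern.** A sensitivity analysis should re-estimate the quantity on which the verdict rests, under a different assumption. Here that quantity is an absolute 2-year rate with its lower confidence limit. Fine-Gray regression estimates how covariates change the subdistribution hazard. When every patient has the same treatment and no covariate is named, there is no coefficient that bears on the question.

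The event wording adds a second difficulty. If recurrence counted as an event in this model, it would be analysing a wider endpoint than the primary one, and 58% is not stated as a benchmark for that.

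What is at stake is how much the verdict depends on deaths from other causes. The event list in 2.7 omits death, so read literally such patients are censored in the Kaplan-Meier estimate. Section 2.2 admits patients with poor performance status or chronic kidney disease, so some other-cause deaths within two years are plausible. The check as named would not show whether they alter the conclusion.

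**Working it through.** **1. The plan's own figure.** Inputs from 2.7: 58% against 90% at 2 years, two-sided α 0.05, power 90%, 3 years' accrual, 2 years' follow-up. Assume exponential survival and uniform accrual.

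- Hazards: λ0 = −ln(0.58)/2 = 0.2724; λ1 = −ln(0.90)/2 = 0.0527.
- Event probability under the alternative: 1 − (e^(−2λ1) − e^(−5λ1))/(3λ1) = 0.1675.
- Cube-root-of-hazard test, variance under the alternative: n = [(1.960 + 1.282) × 0.3749 / (3 × √0.1675) / (0.6482 − 0.3749)]² = 13.11, so 14.
- Allowance: 14/0.8 = 17.5, so 18; 14/0.7 = 20.

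The stated 14 and 20 reproduce. They are not in dispute, and they confirm that the target is one absolute rate.

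**2. Question and method side by side.**

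| | Primary analysis | Sensitivity analysis as named |
|---|---|---|
| Event | A or B (2.7) | described with recurrence as well as progression (2.10) |
| Death | not in the event list | other-cause death competes |
| Output | 2-year rate and 95% CI | subdistribution hazard ratios |
| Comparison with 58% | lower limit above 58% | none given |

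**3. Why the event wording should be aligned.** At the assumed 90% PFS, about 0.10 × 20 = 2 of 20 patients have a primary event by 2 years (0.10 × 14 = 1.4 of 14). The Introduction cites surgical-site recurrence after ablation of 30.7% to 90.5%, which would be 0.307 × 20 = 6.1 to 0.905 × 20 = 18.1 of 20 patients. Those are other cohorts, the article gives no follow-up time for the figures, and the trial aims to lower recurrence. They show only that the two events may differ greatly in frequency.

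**4. What the handling of deaths can do.** The article gives no death rate, so these data are assumed: n = 20, 3 other-cause deaths, then 4 progressions, no other censoring before 2 years. Lower limits are rate − 1.96 × SE.

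- Kaplan-Meier, deaths censored: 17 remain at risk, 13/17 = 76.5%; SE = √(0.765 × 0.235/17) = 0.103; lower limit 56.3%, below 58%.
- One minus cumulative incidence: 1 − 4/20 = 80.0%; SE = √(0.8 × 0.2/20) = 0.089; lower limit 62.5%, above 58%. Equivalently, the upper limit of the cumulative incidence is 37.5%, below 42%.
- Death as an event: 13/20 = 65.0%; SE = 0.107; lower limit 44.1%, below 58%.

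The result depends on the interval scale. With log-log limits the three values are 48.8%, 55.1% and 40.3%, all below 58%.

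**5. Direction over a range.** Assume constant hazards, net 2-year PFS p, and other-cause death d by 2 years. With a = −ln p and b = −ln(1 − d), the cumulative incidence is a/(a + b) × [1 − p(1 − d)], and the rate counting death is p(1 − d).

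| Kaplan-Meier, deaths censored (p) | d | 1 − cumulative incidence | Death as event |
|---|---|---|---|
| 90% | 5% to 30% | 90.2% to 91.6% | 85.5% to 63.0% |
| 80% | 5% to 30% | 80.5% to 83.1% | 76.0% to 56.0% |
| 70% | 5% to 30% | 70.7% to 74.5% | 66.5% to 49.0% |

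For the same event, one minus cumulative incidence is never below Kaplan-Meier with deaths censored. A competing-risk estimate alone can therefore only support or improve on the primary estimate. Counting death moves it the other way.

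**The case against.** The intent is clear: other-cause deaths are to be treated as competing. Fitted without covariates, a Fine-Gray model reduces to the cumulative incidence curve, and one minus that could be set against 58%. Model terms and reported quantities are often left to a full protocol or analysis plan, which is not shown here. This stands in part. It rules out saying that no competing-risk analysis could serve. But the article names a regression, and what a regression reports is not a 2-year rate.

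A reader might infer three stronger things, none of which the document supports.

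- *That the sensitivity analysis deliberately uses a different endpoint.* The model is introduced as an analysis of the primary endpoint. The mention of recurrence occurs in a sentence about which deaths compete, and may be loose wording. It is an inconsistency to clear up.
- *That the plan otherwise has no analysis dealing with deaths.* Section 2.10 refers to survival outcomes among the secondary endpoints in Fig. 1, which is not shown. These may include death.
- *That the damage can be sized by how wide a hazard-ratio interval would be.* No covariate is named, so no planned estimate has such an interval.

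It is also fair to say that the primary verdict does not use this analysis at all.

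**Conclusion.** The point holds in a limited form. For a single-arm question about an absolute 2-year rate, the protocol article names a regression whose usual output cannot be compared with 58%, and it describes the event more widely than 2.7 does. This is a stated method that fits the design poorly, not a detail left to another document.

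The weight is moderate to minor. The Kaplan-Meier rule stands unchanged, and only the robustness check is affected. Handling of deaths may decide a borderline result: in the assumed data the plain lower limits run from 44.1% to 62.5%, either side of 58%. That illustration rests on assumed deaths, their timing before the progressions and plain limits, and the change of verdict disappears with log-log limits. The reading that deaths are censored in the primary analysis rests on the event list in 2.7.

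**What to change.** In 2.10, replace the regression sentence with two analyses, fixed before results are seen.

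1. The Aalen-Johansen cumulative incidence at 24 months of events A/B exactly as in 2.7, with other-cause death competing and a 95% CI. It supports a positive verdict if the upper limit is below 42% (100% − 58%).
2. A 2-year Kaplan-Meier rate counting death from any cause as an event along with A/B, with its 95% CI compared with 58%. This is needed because the first analysis cannot look less favourable than Kaplan-Meier with deaths censored.

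Use the same interval scale in both as in the primary analysis, and say which it is. Align the event wording with 2.7. If a combined outcome of recurrence and progression is wanted, it should carry its own name, unless Fig. 1 already lists it.

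The cost is a few sentences and a little more analysis work, with no change to sample size or data collection. The death-as-event figure may be less favourable. The article does not say whether the historical 58% counted deaths. If it did not, that comparison is a strict one, and the report should say so.
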